### Study Procedures

#### Overview

The study will last 90 days and has two stages. The first stage includes the initial period of using the mHealth devices (Days 1-21) to evaluate the validity of collecting vitality parameters (eg, heart rate, blood oxygenation, steps/motion) on mHealth devices. The main period of use for the mHealth devices (Days 22-90) is the second stage, which aims to evaluate the feasibility of participants using these devices. The schedule of enrollment and data collection is shown in Table 1.

For Table 1, spirometry was performed to diagnose and monitor COPD. Providing of mHealth devices involved the provision of the AnaMed OEM device, the Air Next mobile spirometer, and instructions/review of how to use these tools (print and verbal instructions). For the assessment of the AnaMed OEM device, the participants’ SpO2 will be measured at each visit using industry-standard pulse oximetry devices, and for the assessment of the Air Next spirometer, participants will host the mobile spirometer at home for once daily measurements. Measurements will be validated at Study Center visits using an industry-standard device before and after the use of a bronchodilator.

**Table 1 table1:** Schedule of study activities.

		Device assessment period			Clinical feasibility study period				
	Screening	Baseline visit	Interim visit	Final visit	Interim visits			Final visit	
Visit	1	2	3	4	5	6	7		8
Days	1	7	14	21	28	35	56		90
Informed consent process	✓								
Study eligibility and smoking status	✓								
Reviewing medical history (including physical examination and BMI^a^ measurement)	✓	✓	✓	✓	✓	✓	✓		✓
COPD^b^ assessment test	✓	✓	✓	✓	✓	✓	✓		✓
Spirometry	✓	✓	✓	✓	✓	✓	✓		✓
6-minute walk test	✓	✓	✓	✓	✓	✓	✓		✓
Providing the study requirements handout and explaining the study/visit requirements	✓	✓	✓	✓	✓	✓	✓		✓
Dichotomous questionnaire for visit readiness	✓								
Providing mHealth^c^ devices	✓								
Assessment of AnaMed OEM^d^ device		Continuous monitoring							
Assessment of Air Next mobile spirometer against standard		Continuous monitoring							

^a^BMI: body mass index.

^b^COPD: chronic obstructive pulmonary disease.

^c^mHealth: mobile health.

^d^OEM: original equipment manufacturer.

#### Participant Recruitment and Registration

We will employ various nonprobability sampling techniques, including quota and snowball sampling methods, to recruit study participants. The Kazakhstan Academy of Preventive Medicine research team will register patients for each mHealth device. Installation and user guides for each technology used include labeled photographs and written instructions to be used by all teams and patients during setup. All equipment has been tested before deployment. Training is provided on setup, installation, and use as well as individual checklists, decision trees, and troubleshooting information. The break for charging is at a standard time (20:00) across arms. In addition to direct phone communication, WhatsApp, texting, and other types of messaging systems are used for sharing daily experiences each evening to assist with assessing the level of comfort and address issues with wearing the AnaMed OEM device and using the Air Next mobile spirometer.

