**Methods:**

A total of 3 cohorts, with 9 participants in each, will use mHealth devices for 90 days while undergoing the current standard of care. These groups are: 9 “non-COPD,” otherwise healthy, smokers; 9 “grey zone” smokers (forced expiratory volume in 1 second/ forced vital capacity ≥0.70 after bronchodilator treatment; COPD Assessment Test ≥10); and 9 smokers diagnosed with Stage 1-3 COPD. Rates of recruitment, retention, and adherence will be measured. Overall, two mHealth devices will be utilized in the study: the AnaMed Original Equipment Manufacturer device (measures distance, energy expenditure, heart rate, and heart rate variability) and the Air Next mobile spirometry device. The mHealth devices will be compared against industry standards. Additionally, a questionnaire will be administered to assess the participants’ perceptions of the mHealth technologies used.

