### Outcome Measures

Safety and tolerability will be evaluated through adverse events (AEs), lung function tests, vital signs, and supportive care medications. Primary measures are defined as rates of recruitment, retention, and adherence as well as safety of the intervention that are common for feasibility studies [40]. Recruitment is defined as the number of potential participants screened for study eligibility versus the number of people who enrolled in the study. Retention is defined as the proportion of participants enrolled who completed the intervention and all study measures. Adherence to the study protocol is determined as the proportion of participants enrolled who had all their mHealth parameters registered every day.

The mHealth devices will be compared to the industry standards. Additionally, a questionnaire will be administered to assess the participants’ perceptions of the mHealth technologies used.

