### Sample Size Calculation

The primary endpoints of the study are rates of recruitment, adherence, and retention. To assess the feasibility of the intervention, we plan to recruit 27 participants, which should be enough to get estimates with a sufficient degree of uncertainty. We conservatively predict that 30% of the people invited to participate will be recruited to the study, with a 95% CI of 13-47%. We also assume the dropout rate will be 15%. The accuracy of the estimated retention rate will be at least ±13%. Further, we believe that 70% of participants will adhere to the use of mHealth devices. In this case, the accuracy of the estimate will be at least 17%. All calculations are based on two-way 95% confidence intervals.

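### The primary recruitment rate is open to downward bias from quota closure, because eligible, consenting people screened after their cohort is full count as not recruited

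*Protocol article*

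**What the plan says.** Under Sample Size Calculation the article states: "The primary endpoints of the study are rates of recruitment, adherence, and retention". Outcome Measures defines the first of these: "Recruitment is defined as the number of potential participants screened for study eligibility versus the number of people who enrolled in the study". No screening outcome is set apart for people whose cohort has closed.

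Enrolment is capped. The Abstract gives "A total of 3 cohorts, with 9 participants in each", Study Design repeats the three groups of nine, and Participant Recruitment and Registration states the method: "We will employ various nonprobability sampling techniques, including quota and snowball sampling methods, to recruit study participants".

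Inclusion Criteria separates asymptomatic from grey-zone smokers by CAT score and 6MWT distance, given preserved spirometry. Table 1 first schedules CAT, spirometry and 6MWT at Visit 1, the screening visit, alongside informed consent. Data Management places the eligibility check after consent. The COPD cohort requires a confirmed diagnosis, which a candidate may already have.

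The only planning figure for recruitment has a different denominator, people invited: "We conservatively predict that 30% of the people invited to participate will be recruited to the study, with a 95% CI of 13-47" per cent.

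**The concern.** Three stated rules interact. The rate counts everyone screened, enrolment stops at nine per cohort, and for two of the three cohorts membership is settled by tests done at screening. Once one of those two cohorts is full, the plan has no scheduled step before screening that would divert its further members. A person who consents, meets every criterion and belongs to the full cohort adds one to the screened count and nothing to the enrolled count.

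The Objective and Limitations sections say that the study is meant to show whether a larger study is feasible and to inform its design. A rate lowered by the 9/9/9 caps mixes willingness and eligibility with the order in which cohorts happened to fill. Those who plan the next study could not separate the two unless quota-full cases were logged.

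**Working it through.** **1. The plan's own figure.** The stated interval is p ± 1.96·√(p(1−p)/n). With p = 0.30 and n = 27 the half-width is 1.96·√(0.21/27) = 0.173, giving 12.7% to 47.3%, which matches the stated 13–47%. It contains no allowance for quota closure and refers to people invited, so it is no benchmark for a screened-to-enrolled rate.

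**2. Size of the quota effect.** Inputs from the article: three cohorts, nine each, 27 in all; rate = enrolled/screened. Assumptions, because the article is silent:
- a true proportion p of screened people is eligible and consenting, the same in each cohort;
- cohort is unknown before screening;
- all comers are screened until the last cohort reaches nine;
- the cohort mix is as listed below.

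Let C be the expected number of eligible, consenting people turned away because their cohort is full, and S the expected number screened. Then S = (27 + C)/p, and the recorded rate is 27/S = p × 27/(27 + C). C was found by simulating sequential screening. With p = 0.60:

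| Assumed mix (non-COPD/grey zone/COPD) | C | S = (27 + C)/0.60 | Recorded rate 27/S |
|---|---|---|---|
| Any mix, full cohorts closed to screening | 0 | 45.0 | 60% |
| Equal thirds | 7.8 | 34.8/0.60 = 58.0 | 46.6% |
| 50/20/30 | 19.9 | 46.9/0.60 = 78.2 | 34.5% |

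The factor 27/(27 + C) does not involve p, so the recorded rate stays proportional to the true one. With equal thirds, a true 30% reads 0.30 × 27/34.8 = 23%.

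**3. If COPD status is always known in advance.** Nine COPD participants then need 9/0.60 = 15 screened, with none turned away, and only the other two cohorts (18 people) are sorted at screening.
- Half of the remaining smokers grey zone: C = 3.3, S = 21.3/0.60 + 15 = 50.5, rate 27/50.5 = 53%.
- 30% grey zone: C = 12.1, S = 30.1/0.60 + 15 = 65.2, rate 27/65.2 = 41%.

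The bias shrinks but remains.

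**4. Which correction recovers 60%?** In the all-comers setting of step 2:
- Removing quota-closed people from the denominator: 27/(58.0 − 7.8) = 27/50.2 = 54% with equal thirds, and 27/(78.2 − 19.9) = 27/58.3 = 46% with 50/20/30. This is still biased, because it deletes only would-be successes and keeps the refusals and ineligible people seen in the same period.
- Adding them to the numerator: 34.8/58.0 = 60% and 46.9/78.2 = 60%.

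**The case against.** The strongest reply is that the harmful event is not described. Nothing in the article says that surplus people are screened and refused, and quota sampling can direct invitations to cohorts still open. This stands as a limit on the size: the distortion is zero if full cohorts are closed to screening. It does not remove the point. For asymptomatic versus grey-zone smokers the sorting tests come at the screening visit, so the plan as stated offers no reliable way to close one cohort and not the other.

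A second reply is that Statistical Analysis promises results by study group and Data Management records the reason when a participant is excluded, with the screening-log codes left to the full protocol. The reason field does make the repair easy. But the article itself states the primary definition, and a logged reason does not alter that ratio. Rates by group do not solve it either, since people who leave screening before being classified belong to no cohort.

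Three stronger readings are tempting, and the document does not support them:
- *The rate measures quota closure.* It does not: it remains proportional to true eligibility and willingness.
- *Cohort is unknown before screening for everyone.* A confirmed COPD diagnosis may be known beforehand.
- *Quota closure alone explains the predicted 30%.* A 70/10/20 mix with everyone eligible and willing gives about 27/90 = 30%, but that mix is an arbitrary choice, and the article's 30% is of people invited, not screened.

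**Conclusion.** The point holds as an openness to bias in a stated primary definition. It is not a demonstrated error in a result. The direction is certain: anyone turned away for a full quota can only lower the rate. The size ranges from nothing, if screening closes with each cohort, to a true 60% reading about 47% (equal shares) or about 35% (50/20/30) if all comers are screened until the last cohort fills. Those figures rest on assumed mixes, a common eligibility and consent rate across cohorts, and no prior knowledge of cohort. With COPD known in advance they become about 53% or 41%, for grey-zone shares of 50% or 30% among the remaining smokers. The article does not show that surplus screening will occur, or that a low rate would be misread. It does leave the rate unable to tell quota closure from failure to recruit.

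**What to change.** In Outcome Measures, make eligible and consented with quota closed a separate screening outcome. Define the recruitment rate used for planning as

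(enrolled + eligible and consented but quota closed) / all screened,

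and report the raw enrolled/screened ratio beside it as secondary. Do not instead drop quota-closed people from the denominator, since that leaves part of the bias. The eligibility result must be recorded for people screened after a cohort has filled.

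The cost is one extra code in the screening log and a second reported ratio. No participants or visits are added.

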#### Data Collection

Participants will synchronize their wearable device (AnaMed OEM device) and the Air Next mobile spirometry device by signing into their account. Data are stored in a local cloud system. The entire process of data ingestion and storage has been audited, according to ALCOA (attributable, legible, contemporaneously recorded, original, accurate) standards [41]. Whenever a participant synchronizes new activity data to their device cloud, those data would be ingested, processed, and archived, and then aggregated and summarized in JSON data format by summarization services.

#### Mobile Health Apps

Participants will be provided with a smartphone (iPhone) to perform and visualize measurements and are expected to keep smartphones after the study completion, which will serve as compensation for participation. This is reflected in the Informed Consent Form.

Participants will be guided to assess their health status using the Symptomaster application (HealthCity, Kazakhstan) and zdrav.kz database, which will both also act as tools to determine any potential AEs. The SmartHealth technology Symptomaster helps patients to establish the probable causes of the symptoms of diseases without assistance from a healthcare professional. Using a smartphone, a participant inputs his/her symptoms into the system, which then produces the most likely preliminary diagnosis. After receiving the diagnosis, a patient can refer to zdrav.kz, an online library that contains information about the 1000 most common diseases and their causes and symptoms, in addition to ways to prevent and treat them. These technologies allow a participant to make an informed decision about whether they should seek immediate medical assistance by calling an ambulance or if they should consult a doctor on their next routine visit.

#### Physical Examination

Physical examinations will be conducted during each visit based on the Stanford Medicine 25 comprehensive clinical assessment to identify clinical signs of abnormalities. This will be in addition to standard anthropometric measurements and vital sign assessments (pulse rate, blood oxygenation, and blood pressure).

#### Spirometry

The Air Next mobile spirometer will be used by patients to assess respiratory function. To use it, patients must hold their hands on tubular grips or use wrist clamps. Subsequent respiratory efforts allow the determination of inspiratory capacity and FEV_1_. Participants are categorized for analysis using the GOLD staging system according to their spirometry, which will be performed before and after two inhalations of salbutamol (0.1 μg per inhalation). Among the criteria needed to make a diagnosis of COPD are deficits in the rate at which one can forcefully exhale. Most experts consider a low ratio (<0.70) of the FEV_1_ to the FVC after bronchodilator use to be a key diagnostic criterion. Bronchodilator responsiveness will be considered positive if the participant has a ≥12% change in FEV_1_ or FVC above prebronchodilator measurements.

#### Six-Minute Walk Test

This test measures the distance that a patient can quickly walk on a flat, hard surface in 6 minutes. A 100-feet hallway is needed, and no exercise equipment or advanced training for technicians is required.

#### Physical Activity

Study participants will measure their pedometer-determined physical activity using the AnaMed OEM wearable devices. While performing the six-minute walk test, participants will simultaneously use the AnaMed OEM and Garmin Vivo (Garmin Ltd, Olathe, Kansas, United States) devices to compare step counts from both devices.

#### Chronic Obstructive Pulmonary Disease Assessment Test

The CAT is used as an add-on test with existing assessments in COPD (eg, with FEV_1_). It is a simple and reliable measure of health status in COPD as it assists patients and their physicians in quantifying the impact of COPD on the patient’s health. The CAT is a validated, short (8-item) questionnaire to be completed by patients.

#### User Experience Questionnaire

Participants will be administered questionnaires to assess their mHealth device use experience. One questionnaire is administered for each device. The questions will address comfort levels and ease of daily vital measurements. The interviews will be conducted by clinical investigators not involved with the quantitative monitoring or analysis to reduce the possibility of bias.

### Data Management

All study data will be stored in the information technology Unit of the Kazakhstan Academy of Preventive Medicine. Verification of eligibility was completed via a web questionnaire after participants signed the consent form, and participants will be tracked for the completion of all the study data. If a participant is excluded or discontinues use during or after the study procedures, the specific exclusion or discontinuation reason will be recorded in the database.

All electronic files are encoded using a 128-bit advanced encryption standard and are password protected on a computer with both hardware and software firewalls. The locator form and any documents with identifying information are kept in a separate folder and kept locked in filing cabinets.

### Statistical Analysis

For this proof-of-concept phase, access to device-derived data will be enabled via a cloud-to-cloud solution. Graphical and statistical comparisons will be made between the mobile biosensing device–derived data and the data derived from the clinical standards, and between the three different study groups. Descriptive statistics will be used to summarize required qualitative and quantitative study elements (eg, proportion, mean, standard error, median, interquartile range, 95% confidence interval).

The exploratory graphical analysis will be done before the numerical analysis. Histograms and two-dimensional scatterplots of raw data will provide information on the univariate and bivariate distributions of the variables, focusing on the distribution of variables and relationships between the variables (whether there is a linear or nonlinear relationship). Additionally, preliminary graphs will be used to screen raw data by highlighting obvious data errors. Tabulations will be produced for appropriate disposition, demographics, baseline, safety, and clinical parameters.

Statistical comparisons will be made between the mobile biosensing device–derived data and the data derived from the standard diagnostic equipment and methods. Agreement analysis will be performed for both binary and quantitative measures. For binary variables, percent of agreement (overall, positive, and negative agreement) as well as Kappa coefficient, *P* value, and 95% confidence interval will be calculated. For two quantitative measures of a parameter, we will use the Bland-Altman method (Bland-Altman plot and limits of agreement). The Bland-Altman plot analysis will allow us to evaluate a bias between the mean differences and to estimate an agreement interval, within which 95% of the differences between two quantitative methods of measurement are included. Correlation analysis will also be run so that Pearson’s correlation coefficient and the 95% confidence interval will be calculated.

The agreement analysis will be done for baseline, 7-day, 14-day, 21-day, 28-day, 56-day, and 90-day visits separately and for the data pooled from all measurements. Within-Subject study design will be accounted for to assess accuracy and precision for a single mobile device. All statistical analyses will be done for all participants and by study group. Additionally, we will compare trends of binary and quantitative outcomes from three study groups wearing mobile devices.

The analysis will be performed using R Statistical Software (R Foundation for Statistical Computing, Vienna, Austria).

### Ethics Approval

The Ethics Committee of the Academy of Preventive Medicine approved this study on June 3, 2019. The study has been registered at ClinicalTrials.gov (NCT04081961).

## Results

The inclusion of the participants started in June 2019. Study results will be published in peer-reviewed scientific journals.

## Discussion

### Principal Considerations

The proposed study is the first step in a series of studies aiming to investigate the effect of using mHealth devices to improve the treatment, assessment, compliance, and outcomes of smokers with and without respiratory symptoms/COPD. The results from this proof-of-concept, open-label, device feasibility study will be used to finalize the protocol for a randomized, open-label, placebo-controlled, single-center, two-arm, 12-month study designed to assess clinical feasibility and the effect of this intervention.

### Limitations

This study is a small-scale, exploratory, pilot study which is looking to answer questions about whether a larger trial is feasible or not and seeks to get estimates of parameters required for the calculation of the sample size of the main study. The results of this study cannot be used to estimate the effect size of using mHealth devices because the sample size is too small.

### Conclusion

Many studies have shown that mHealth tools are effective or that they provide accurate disease recommendations. This study will demonstrate whether a large-scale study to assess the use of mHealth devices to improve the treatment, assessment, compliance, and outcomes of chronic diseases, particularly COPD and cardio-metabolic syndrome, is feasible, and will also allow for the selection of an appropriate design and characteristics for the later large-scale study.

## Abbreviations

6MWT: six-minute walk test
AE: adverse event
CAT: Chronic Obstructive Pulmonary Disease Assessment Test
COPD: chronic obstructive pulmonary disease
eHealth: electronic health
FEV_1_: forced expiratory volume in 1 second
FVC: forced vital capacity
GOLD: Global Initiative for Chronic Obstructive Lung Disease
mHealth: mobile health
OEM: original equipment manufacturer
SpO2: peripheral capillary oxygen saturation
